#### Transient Ischemic Attacks (TIA)

A TIA is defined as a rapid onset of a focal neurological deficit that resolves spontaneously without evidence of residual symptoms at 24 hours.

#### Acute Myocardial Infarction

Any one of the following criteria meets the diagnosis for myocardial infarction (MI).

1. Detection of elevated values of cardiac biomarkers (preferably troponin T or I) above the 99th percentile of the upper reference limit (URL) together with evidence of myocardial ischemia with at least one of the following:

· Ischemic symptoms;

· ECG changes indicative of new ischemia (new ST-T changes or new left bundle branch block [LBBB]);

· Development of pathological Q waves in the ECG;

· Imaging evidence of new loss of viable myocardium or new regional wall motion abnormality.

2. Sudden unexpected cardiac death, including cardiac arrest, with symptoms suggestive of myocardial ischemia, or accompanied by new ST elevation, or new LBBB, or definite new thrombus by coronary angiography but dying before blood samples could be obtained, or in the lag phase of cardiac biomarkers in the blood.

3. For percutaneous coronary intervention (PCI) in patients with normal baseline values, elevations of cardiac biomarkers above 99th percentile of the URL are indicative of peri-procedural myocardial necrosis.

4. For coronary artery bypass graft (CABG) in patients with normal baseline values, elevations of cardiac biomarkers above the 99th percentile of the URL are indicative of peri-procedural myocardial necrosis. By convention, increases of biomarkers greater than 5 × 99th percentile of the URL plus either new pathological Q waves or new LBBB, or angiographically documented new graft or native coronary artery occlusion, or imaging evidence of new loss of viable myocardium have been designated as defining CABG-related MI.

5. Pathological findings post-mortem of an acute MI.

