## Methods

### Study design

#### Outcome measures

The first primary endpoint for TIOSPIR® is all-cause mortality. Clinical sites follow all randomized patients for vital status until trial conclusion, including patients who prematurely discontinued study medication, and collect medical information regarding the date and cause of fatal events.

The second primary endpoint for TIOSPIR® is time to first COPD exacerbation. COPD exacerbations are defined as a complex of two or more respiratory symptoms (worsening dyspnea, cough, sputum production, chest tightness, or wheezing) related to the underlying COPD, with duration of 3 days or more, that require a change in treatment. Treatment changes include acute treatment with antibiotics and/or steroids, or an addition of new maintenance bronchodilator. Mild exacerbations are those that require new prescription of bronchodilator only, moderate exacerbations are those that require antibiotics and/or systemic corticosteroids without hospitalization, and severe exacerbations are those that lead to hospitalization. The onset date of exacerbations is defined by the onset of the first recorded symptom. Exacerbations that occur within 7 days of onset of a prior exacerbation are counted as a single exacerbation.

Secondary outcome measures will also be analyzed by treatment group to support inferences derived from the primary analysis. These measures include the number of COPD exacerbations, the time to first exacerbation associated with hospitalization, the number of exacerbations associated with hospitalization, and the time to the first major adverse cardiovascular event (e.g. fatal event in system organ classes cardiac and vascular disorders, myocardial infarction [MI], or stroke). Criteria for definition of major adverse cardiovascular events are specified in the protocol and are adjudicated by the site investigator who is masked to the study treatment (see Appendix). In a subset of approximately 1300 patients, spirometry was conducted at baseline and is repeated every 24 weeks. Patients in the substudy perform pulmonary function tests at a single time point in triplicate to record trough FEV_1_ and forced vital capacity (FVC). Tertiary analyses of treatment groups will be performed on subgroups specified by demographic variables, co-morbid conditions, disease severity, and concomitant medications.

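### The appendix gives no rule that defines a PCI-related MI, so under the any-one-criterion heading an isolated biomarker rise after PCI counts as an MI in the secondary MACE outcome

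*Protocol article*

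**What the plan says.** The Protocol article, under Outcome measures, lists as a secondary outcome "the time to the first major adverse cardiovascular event (e.g. fatal event in system organ classes cardiac and vascular disorders, myocardial infarction [MI], or stroke". It adds that masked site investigators judge these events, and it refers the reader to the Appendix for the definitions.

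The Appendix section on acute myocardial infarction has five items under one combining rule: "Any one of the following criteria meets the diagnosis for myocardial infarction (MI". Three of the items matter here.

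- **Item 1** requires a biomarker value above the 99th percentile of the upper reference limit (URL) "together with evidence of myocardial ischemia with at least one of the following", followed by a list of symptoms, ECG changes and imaging findings.
- **Item 3** begins "For percutaneous coronary intervention (PCI) in patients with normal baseline values" and ends "elevations of cardiac biomarkers above 99th percentile of the URL are indicative of peri-procedural myocardial necrosis". Nothing follows.
- **Item 4**, on CABG, has a near-identical first sentence: "elevations of cardiac biomarkers above the 99th percentile of the URL are indicative of peri-procedural myocardial necrosis". It then adds a second one: "increases of biomarkers greater than 5 × 99th percentile of the URL plus either new pathological Q waves or new LBBB", or angiographic or imaging evidence, "have been designated as defining CABG-related MI".

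**The concern.** A list in which any one item is enough works only if each item states what makes an MI. Item 3 does not. It describes a sign of necrosis, and the heading turns that sign into a diagnosis. After PCI, a patient with an isolated rise and no evidence of ischemia would be recorded as having had an MI.

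The trial was set up because of a safety question about one inhaler, and it admits patients with stable cardiac disease. MACE is its named cardiovascular outcome. Events that come from a procedure and from local biomarker testing, and not from the inhaler, would be expected at similar rates in all arms. Adding them moves the hazard ratio towards 1, which in a safety comparison is the direction that hides a difference. Because the outcome is time to first event, such an entry also displaces any later genuine event in the same patient.

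The written definition carries much of the weight. The article describes a central committee for deaths but no central review of non-fatal MI. The criteria are applied at more than 1200 sites, many of them run by community practitioners.

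**Working it through.** No figure in the article depends on this point. The 1266 deaths and 16,800 participants under Sample size and power rest on all-cause mortality. The check is therefore a comparison of the items, followed by an illustration of size.

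**Step 1: the items side by side**

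| Item | Biomarker threshold | Baseline condition | Further evidence required | Does the item say what defines MI? |
|---|---|---|---|---|
| 1, general | above 99th percentile of URL | none stated | yes, ischemia (at least one listed finding) | yes |
| 3, PCI | above 99th percentile of URL | normal | none | no, necrosis only |
| 4, CABG, first sentence | above 99th percentile of URL | normal | none | no, necrosis only |
| 4, CABG, second sentence | more than 5 × 99th percentile | normal (from the item's opening) | yes, ECG, angiographic or imaging | yes |

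**Step 2: three test cases**

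- *PCI, normal baseline, value at 2 × the 99th percentile, no symptoms, ECG or imaging finding.* Item 1 is not met. Item 3 is met as written, so under the combining rule this is an MI. The alternative is to read item 3 as describing necrosis only. It then defines nothing, and a listed criterion is empty. The item needs correction on either reading.
- *CABG, same values, no other finding.* Item 4 read as a whole gives necrosis but not CABG-related MI, because its second sentence is expressly the defining one. A site that stops at the first sentence and applies the heading could still record an MI.
- *PCI, biomarkers already raised beforehand.* Item 3 does not apply.

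**Step 3: size, on assumed values**

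Let f be the share of comparator-arm MACE that are procedural rises unrelated to treatment and equally frequent in both arms. The article gives no PCI, CABG or MACE rate, so f is an assumption. The hazard ratio that would be seen is then approximately

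HR(seen) = (1 − f) × HR(true) + f

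| f | True HR 1.25 | True HR 1.50 |
|---|---|---|
| 0.01 | 0.99 × 1.25 + 0.01 = 1.2475 | 0.99 × 1.50 + 0.01 = 1.495 |
| 0.05 | 0.95 × 1.25 + 0.05 = 1.2375 | 0.95 × 1.50 + 0.05 = 1.475 |
| 0.10 | 0.90 × 1.25 + 0.10 = 1.225 | 0.90 × 1.50 + 0.10 = 1.450 |
| 0.20 | 0.80 × 1.25 + 0.20 = 1.200 | 0.80 × 1.50 + 0.20 = 1.400 |

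The dilution is negligible at the low end and modest at the high end.

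**The case against.** Two stronger readings are tempting, and the text supports neither.

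- A reader might infer that item 4 contradicts itself. It does not. Its first sentence speaks of necrosis and never calls the rise an MI, and its second states what defines CABG-related MI. What remains is an ambiguity, created by placing an unqualified necrosis sentence under a heading that makes any one criterion sufficient.
- A reader might infer that every biomarker rise after a procedure becomes an MI. Items 3 and 4 are limited to patients whose values were normal beforehand. Moreover, a procedure that follows an MI already counted as MACE adds nothing to a time-to-first-event outcome.

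Three further objections deserve an answer.

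- The article says the criteria are specified in the protocol, which is not shown. A defining sentence for PCI may exist there, so it cannot be established that sites lacked one. This limits what can be claimed about conduct, but it does not excuse the printed text. The appendix sets the definition out item by item, and the criticism is of what it states.
- Masked judgement should keep misclassification from differing by arm. That stands. It does not stop equal numbers of unrelated events from diluting a difference.
- The effect is small and touches no primary conclusion. That also stands. The confirmatory hierarchy contains two mortality tests and one exacerbation test, and MACE is not in it.

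**Conclusion.** The point holds for PCI. As printed, item 3 supplies no rule that defines a PCI-related MI, and the combining rule makes an isolated rise above the 99th percentile, in a patient with normal baseline values, sufficient by itself. That is looser than item 1 and disregards the distinction between necrosis and MI that item 4 draws. For CABG the defect is ambiguous drafting only.

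The consequence is confined to the secondary MACE outcome. Its size cannot be derived from the article. The range of about 1.248 to 1.20 for a true hazard ratio of 1.25 rests on assumed shares of 1% to 20% and on procedural rises being equally common in the arms. The wording should be corrected because it states a rule that would misclassify events, but the primary analyses do not depend on it.

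**What to change.** Reconcile items 1, 3 and 4 of the MI definition:

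1. Mark the necrosis sentences in items 3 and 4 as explanatory and not sufficient for a diagnosis of MI.
2. State that, for CABG, only the defining sentence counts.
3. Give PCI-related MI a defining rule of its own. The threshold is for the sponsor to choose.
4. If the necessary values were collected (baseline and post-procedure biomarkers and local reference limits), apply the rule to reported peri-procedural MIs before unblinding, with reviewers masked to treatment. If they were not, say so when MACE is reported.

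Steps 1 to 3 cost a change to the appendix and a note to sites. Step 4 may cost more than it appears, because the article does not show that these data were recorded and there are more than 1200 sites. The price in the analysis is slightly fewer counted MIs.

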## Abbreviations

COPD: Chronic obstructive pulmonary disease; CI: Confidence interval; DMC: Data Monitoring Committee; DPI: Dry powder inhaler; FEV_1_: Forced expiratory volume in 1 second; FVC: Forced vital capacity; HR: Hazard ratio; IR: Incidence rate; MAC: Mortality Adjudication Committee; MI: Myocardial infarction; PK: Pharmacokinetic; SMI: Soft Mist™ Inhaler; SSC: Scientific Steering Committee; TIOSPIR®: TIOtropium Safety and Performance In Respimat®; UPLIFT®: Understanding Potential Long-term Impacts on Function with Tiotropium.
